## Abstract

**Background:**

Poor dietary habits are common among childhood cancer survivors, despite increasing their risk of cardio metabolic complications after cancer treatment. Here, we describe the design and rationale for a pilot telephone-based, parent-led intervention aimed at increasing fruit and vegetable intake in young cancer survivors (Reboot).

**Objective:**

This pilot study aims to assess the feasibility and acceptability of delivering evidence-based telephone support to parents of childhood cancer survivors. A secondary aim includes assessing the effect of Reboot on improving childhood cancer survivors’ dietary quality by increasing child fruit and vegetable intake and variety and its contribution to overall nutrient intake.

**Methods:**

We aim to recruit parents of 15 young cancer survivors aged 2 to 12 years who have completed cancer treatment less than five years ago. The intervention comprises of 4 weekly 45-minute telephone sessions led by a health professional and one booster session 6 weeks later. Sessions address the effects of cancer treatment on children’s diets, recommended fruit and vegetable intake for children, and evidence-based strategies to promote the consumption of fruit and vegetables as well as to manage fussy eating.

**Results:**

Reboot is based on an existing, evidence-based parent nutrition intervention and modified for childhood cancer survivors following extensive collaboration with experts in the field. Primary outcomes of feasibility and acceptability will be measured by the number of participants who complete all five sessions, average session length (minutes), length between sessions (days) and parent Likert ratings of the usefulness and impact of the intervention collected after the booster session. Of the 15 participants we aim to recruit, 3 have completed the intervention, 1 declined to participate, 11 are actively completing the intervention and 2 participants are providing written consent. The remaining 3 participants will be recruited via telephone follow-up calls. The intervention is due to be completed by July 2018.

**Conclusions:**

Reboot aims to support healthy dietary behaviors in childhood cancer survivors who are at increased risk of developing serious cardiometabolic complications after their cancer treatment. Results will inform the development and implementation of future evidence-based dietary interventions delivered to childhood cancer survivors, particularly those living in rural and remote areas.

**Registered Report Identifier:**

RR1-10.2196/9252

## Introduction

The cardiotoxic effects of chemotherapy and radiation have been shown to contribute to an increased risk of cardiovascular disease in survivors of childhood cancer [1]. Consequently, childhood cancer survivors (CCS) are more than six times more likely to experience serious cardiac conditions compared with their siblings, with rates continuing to increase as late as thirty years after cancer treatment [2].

One of the key predisposing factors for cardiovascular disease is metabolic syndrome, a cluster of conditions which includes central obesity, dyslipidemia, glucose intolerance and hypertension [3]. There is a strong association between a diet low in fruit and vegetables and high in saturated fat and sugar, and the onset of metabolic syndrome in CCS [4]. Consequently, CCS with metabolic syndrome are twice less likely to meet national dietary guidelines compared with those who do not have the syndrome [4].

Despite their increased risk of developing serious chronic health conditions, young CCS often report poor health-protecting behaviors [5-8] (eg, reduced intake of fruit and vegetables, excessive energy, and inadequate calcium and folate intake) [9] and a higher intake of non-core (“junk”) foods compared with prediagnosis [10]. These behaviors often develop during treatment when children’s home food environment and eating are disrupted by frequent hospital admissions and treatment related side-effects including nausea, increased appetite, and vomiting [11]. Unhealthy eating habits established during cancer treatment also appear to be exacerbated by parents of CCS who report using unhealthy food as a means to reduce children’s pain and emotional distress after cancer treatment [10,11].

Although dietary behaviors are among the most easily modifiable factors for reducing the risk of cardio metabolic complications, CCS and their families often live long distances from their tertiary hospital [12] making it difficult for health professionals to provide ongoing nutritional support after treatment completion. Telephone interventions may therefore represent a feasible and acceptable approach for promoting healthy eating habits among CCS.

Telephone-based parent-led interventions have successfully increased fruit and vegetable intake in children not previously treated for cancer [13-17]. However, the feasibility and acceptability of telephone-based, parent-led fruit and vegetable interventions in CCS is yet to be evaluated. Therefore, we aim to assess the feasibility and acceptability of delivering evidence-based telephone nutritional support to parents of CCS.

## Methods

### Recruitment

We aim to recruit the parents of 15 CCS. This number is sufficient to provide exploratory findings to inform the design of a randomized controlled trial (RCT) in this population [18]. Based on our previous research, we assume a response rate of 50% and attrition rate of 20% [18-20], and therefore it was anticipated that approximately 50 parents will need to be contacted to recruit 15 families.

Parents will be eligible to participate if they have a child aged between 2-12 years who completed cancer treatment at the Sydney Children’s Hospital (SCH), Randwick, NSW, with curative intent, achieved remission less than 5 years ago and meet the following criteria which are (1) to provide informed consent, (2) be able to read English, and (3) have regular telephone access. Parents will be ineligible if they have (1) insufficient English language skills to complete telephone sessions and or baseline and follow-up assessments, (2) severe depression or suicidal ideation, as determined by the clinical experience of the treating oncologist, or if their child who had cancer, (3) is currently on active treatment or receiving supplementary feeding, (4) has relapsed, (5) is in palliative care or is deceased, or (6) completed cancer treatment more than five years ago.

Eligible participants will be recruited via mail using an information and consent form explaining the purpose of the project and details of participation. Participants can choose to participate by returning the consent form or by contacting the study coordinator. Nonrespondents will be contacted by study personnel via telephone or text message. This protocol was approved by the Network Human Research Ethics Committee (HREC/15/SCHN/395).

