### Statistical Analyses

Data will be analyzed using the Statistical Package for the Social Sciences, version 18.0 (SPSS Inc, Chicago, IL, USA). The primary outcome measure (number of participants who complete all 5 intervention sessions) will be analyzed using a repeated measures design. An 80% study compliance and 20% attrition rate [18] will be used as the benchmark for program feasibility. Cochran *Q* will be used to identify participants as meeting the specific study completion criterion. The secondary outcome measure is the difference in the mean number of fruit and vegetable serves consumed by CCS (on the previous day) from baseline to the end of the intervention (after the booster session). Paired *t*-tests will be conducted to determine whether there is a significant difference between the mean intakes of fruit and vegetable serves at baseline compared to the end of the intervention.

Postintervention Acceptability Items.

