## Results

Initial planning for Reboot Kids began in 2015 via a collaboration with the developers of the ‘Good for kids: Healthy Habits program’ at the University of Newcastle [15]. Healthy Habits is an evidence-based fruit and vegetable program delivered to nearly 400 Australian families. With their consent, our team updated the original parent guidebook to include the most recent version of the Australian Dietary Guidelines and Nutrition Australia Healthy Eating Pyramid, and dietitian approved recipes. To promote immediate and long-lasting intervention changes, we also followed recommendations by the original developers to focus on parent providing of fruit and vegetables to CCS, which mediated the short-and-long-term effectiveness of the intervention [22]. We therefore modified the initial behavior change technique from parenting self-monitoring of CCS daily fruit and vegetable intake to occasions of parent providing of fruit and vegetables to CCS over three days (Table 1).

Ethics approval was obtained on 11th November 2015 (HREC/15/SCHN/395) and recruitment commenced in August 2016. Of the 20 participants we aim to recruit, 7 have completed the intervention (including the booster session), 1 declined to participate after consenting, 2 participants dropped out after completing the first session, 8 are actively completing the intervention and 3 participants are providing consent. We aim to recruit the remaining participants via telephone follow-up calls and complete the intervention by July 2018.

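### The 50 contacts do not follow from 15 families at 50% response and 20% attrition (30 or 38 would), and the recruitment target is 15 in the Abstract and Methods but 20 in the Results

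*Protocol article*

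**What the plan says.** All references are to the protocol article.

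- **Target, Abstract (Methods):** "We aim to recruit parents of 15 young cancer survivors aged 2 to 12 years".
- **Target, Methods, Recruitment:** "We aim to recruit the parents of 15 CCS".
- **Yield assumptions, same section:** "we assume a response rate of 50% and attrition rate of 20" per cent, attributed to earlier research.
- **Conclusion drawn from them, same sentence:** "it was anticipated that approximately 50 parents will need to be contacted to recruit 15 families".
- **Status, Abstract (Results):** "Of the 15 participants we aim to recruit, 3 have completed the intervention, 1 declined to participate, 11 are actively completing the intervention". Two more are giving written consent, and three remain to be recruited by telephone.
- **Status, main Results section:** "Of the 20 participants we aim to recruit, 7 have completed the intervention". One declined after consenting, two left after the first session, eight are in progress and three are giving consent. The section still speaks of further participants to be recruited.
- **Feasibility benchmark, Statistical Analyses:** "An 80% study compliance and 20% attrition rate [18] will be used as the benchmark for program feasibility".

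**The concern.** The contact figure is presented as the result of the target and the two rates, so a reader should be able to reproduce it. It cannot be reproduced for 15 families, and no other input is given, such as a share of parents who cannot be reached or prove ineligible, that would raise the number to 50.

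The target then changes from 15 to 20 between sections of the same current text, without comment. The article does not say whether either number counts families who consent or families who stay to the end.

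Two things are at stake. First, the planned size of the study is uncertain: if the targets are read as families recruited, 20% attrition leaves about 12 or about 16 for the paired comparison. Second, the Discussion says the feasibility data will inform a randomized trial. Fifteen families from 50 contacts is a yield of 30%, whereas the stated rates imply 50% recruited or 40% retained per contact. A planner who took the printed sentence at face value would carry the wrong yield forward.

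**Working it through.** **Inputs.** Target T = 15 (Abstract; Recruitment) or 20 (main Results). Response r = 0.5 and attrition d = 0.2 (Recruitment). Stated contacts: about 50.

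**Formulas.** Contacts to recruit T families = T/r. Contacts to retain T families = T/(r × (1 − d)).

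| Target | To recruit T | To retain T |
|---|---|---|
| 15 | 15/0.5 = 30 | 15/(0.5 × 0.8) = 37.5, so 38 |
| 20 | 20/0.5 = 40 | 20/(0.5 × 0.8) = 50 |

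**Attempts to reproduce 50 from 15.**
- Neither standard formula does so. Against 30, the stated figure is 20 too high (20/30 = 67%). Against 38, it is 12 too high (12/38 = 32%).
- Inflating by a fifth instead of dividing by 0.8 gives 15 × 1.2/0.5 = 36.
- Subtracting the rates gives 15/(0.5 − 0.2) = 50, but this is not valid. It takes the 20% attrition from everyone contacted, when it applies only to those who consent.
- Working backwards, 50 contacts yield 15 families only if the response is 15/50 = 30% with no attrition, or 15/(50 × 0.8) = 37.5% with 20% attrition. Neither is the stated 50%.

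**What 50 contacts give under the stated rates.** 50 × 0.5 = 25 consenting; 25 × 0.8 = 20 retained.

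**Status counts.**

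| | Abstract (stated target 15) | Main Results (stated target 20) |
|---|---|---|
| Completed | 3 | 7 |
| Declined | 1 | 1 (after consenting) |
| Dropped out after session 1 | none listed | 2 |
| In progress | 11 | 8 |
| Giving consent | 2 | 3 |
| Sum | 17 | 21 |
| Sum without the parent who declined | 16 | 20 |
| Still to recruit | 3 | number not given |

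In the Abstract, 17 + 3 = 20, or 19 without the parent who declined. Even that smaller count exceeds 15. In the Results, 7 + 2 + 8 = 17 parents had already started, which also exceeds 15. The Abstract reaches 20 only if the parent who declined is counted, and the Results only if that parent is left out. The different numbers of completers may simply reflect different dates; the different targets are the contradiction.

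**What the 20 in the Results counts.** The sentence speaks of participants to recruit, and the tally of 20 includes the two who dropped out. It therefore reads as 20 recruited, which needs 40 contacts and leaves 20 × 0.8 = 16 retained.

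**The case against.** **A forecast, hedged and on the safe side.** The contact number is a logistics estimate, qualified as approximate, in a single-group pilot whose size is justified by citation and not by power. Approaching more parents than needed harms no analysis, and recruitment was well advanced. This stands and limits the severity. It does not rescue the figure, since no rounding covers a gap of 12 or 20 contacts, and it does not explain two targets.

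**The two targets might be one plan seen at two stages.** Retaining 15 at 20% attrition requires 15/0.8 = 18.75, so 19 recruited, which is close to 20. But the article uses the verb recruit for both numbers, and this reading would need 38 to 40 contacts, still not 50.

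**Stronger readings that the article does not support.**
- A reader might infer that the true plan was 20 retained, because 50 contacts give exactly that. Only the numeral agrees. The Results speak of recruiting 20 and count two dropouts among them. Rewriting the plan as 25 consenting and 20 retained would bring in a target of 25 that appears nowhere.
- A reader might infer that the target sets the pass mark (12 of 15 or 16 of 20), so that the choice between them could be made after losses were known. The benchmark is stated as percentages and is not tied to a target. With 17 parents already started, a denominator of 15 is no longer available. Any count of losses still permitted also depends on whether the parent who declined after consenting is included: three losses with, two without. Nothing in the text links the change of target to the benchmark.

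**Conclusion.** The point holds as an error of arithmetic together with a contradiction in the stated sample size. From 15 families, 50% response and 20% attrition, the number of contacts is 30 (to recruit) or 38 (to retain); 50 exceeds these by 67% and 32%. The target is 15 in the Abstract and Recruitment and 20 in the Results, and neither status tally fits 15.

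The arithmetic assumes that attrition applies to families who have consented, and that no unstated loss occurs between contact and response. That the 20 means families recruited follows from the wording and tally in the Results; the article does not define it. Whether the 50 came from subtracting the two rates or from a different target cannot be determined.

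The severity is moderate. The sample size and recruitment yield are wrong as written, but the figure of 50 enters no analysis and the primary benchmark does not depend on it.

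**What to change.** 1. State one target with its unit, recruited or retained, and use it in the Abstract, Methods and Results.
2. Give the matching number of contacts: 30 to recruit 15, 38 to retain 15, 40 to recruit 20, or 50 to retain 20.
3. If the Results are right, the Recruitment text would say that about 40 parents are approached to recruit 20, of whom about 16 are expected to be retained. If 15 recruited was the plan, say that it has been exceeded and why.
4. Reconcile the two status tallies with the chosen target, and treat the parent who declined in the same way in both.
5. Say that the 80% compliance and 20% attrition benchmark is applied to those actually enrolled.

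**Cost.** Wording only, if the target is 20 recruited. A target of 20 retained would cost more. Of the 20 parents in the Results apart from the one who declined, two have left, so at most 18 can be retained. At least two more would be needed, and the assumed rates imply about 25 consenting in all (20/0.8).

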### Intervention

Reboot models a previous intervention aimed at increasing fruit and vegetable intake in over 400 Australian children (who did not receive cancer treatment) [16]. Following a parent-led interventional model, the parent (not the child) receives the intervention and is responsible for regulating the home food environment and acting as an important role model, which maintains children’s eating behaviors [21].

In line with the original intervention, Reboot will be delivered to only one parent by a trained health professional (either a registered psychologist or dietitian) via 4 weekly 45-minute telephone sessions, with the addition of 1 booster session 6 weeks after the fourth intervention session (Figure 1). Intervention sessions will be guided by a parent guidebook (Figure 2) focusing on key factors associated with increased intake of fruit and vegetables in children, including the accessibility of fruit and vegetables in the home, parental providing and modelling of fruit and vegetable intake, and positive family-based mealtime practices (eg, eating together) [22]. Further details are shown in Table 1.

**Figure 1 figure1:**
[figure not shown]
Reboot Kids study flowchart.

**Figure 2 figure2:**
[figure not shown]
Excerpts from the Reboot Kids parent workbook.

**Table 1 table1:** Reboot intervention session objectives and cancer-relevant content (CCS: childhood cancer survivors).

Weekly session	Core objectives and skills	Cancer relevant content
Introduction and overview	Understanding the rationale for intervening or eliciting motivation. To promote mastery by normalizing parents’ concerns and fears. Understanding the Australian Guide to Healthy Eating and portion sizes. Information about the type and quantity of fruits and vegetables that children should be eating. Identify ‘non-core’ foods and strategies to reduce non-score food intake. Understanding the importance of parent providing fruit and vegetables throughout the day. Introduction of the parent vegetable providing diary to encourage parent self-monitoring of the number of occasions parents provide fruit and vegetables to children throughout the day. Setting specific and achievable program goals.	Importance of supporting healthy eating habits and regular physical activity after cancer treatment. Common experiences of children and parents during and after cancer treatment (eg, food aversions, poor fruit and vegetable intake, altered taste perceptions, physical inactivity, and parent overprotectiveness). End of cancer treatment is one of the most difficult times for families. Addressing challenges (eg, effects of treatment on re-establishing a normal routine, including fatigue, fussy eating, inconsistent discipline, misbehavior, and overprotectiveness).
The home food environment	Identify barriers to introducing change (establishing rules and coping with change). Tips for structuring family mealtimes. Providing praise and positive reinforcement. Brainstorm effective non-food rewards. Review strategies for creating a healthy home environment. Introduce meal planning. Plan for the week ahead.	Addressing challenges for families establishing change after cancer (eg, parent guilt and or overprotectiveness, misbehavior resulting from absence of discipline, and routine during treatment).
Encouraging children to eat vegetables	Practical strategies for promoting fruit and vegetables to children (eg, planning and providing choices). Tips on making food exciting and interesting. Preparing for misbehavior. Discussion of unhelpful strategies (what to try and what to avoid). Understanding the importance of role modelling healthy eating habits to children.	N/A
Consolidation	Review topics from the previous four weeks. Strategies for shopping with children. Review program goals. Preparing for future challenges.	Address any parent fears and or concerns moving forward.
Booster	Review program goals and progress (eg, CCS fruit and vegetable intake, parent-providing, and role modelling of fruit and vegetable intake to CCS). Introduce screen time guidelines. Introduce sleep guidelines. Harnessing support from family and friends.	Re-addressing challenges for families establishing behavior change after cancer, including other caregivers

### Treatment Late Effects

A study by our team identified a significant proportion (>90%) of Australian and New Zealand parents reporting unmet needs for information about the late effects of cancer treatment [23]. An introductory information module (“*Why is healthy eating important for children after cancer treatment?* ”) was developed to increase parents’ knowledge about the most common serious long-term health problems identified among childhood cancer survivors (eg, weight gain, heart disease, diabetes, high blood pressure, and high cholesterol) and evidence-based behaviors that may help to prevent or reduce occurrence of treatment late effects (eg, increasing children’s intake of fruits and vegetables).

### Changes in Parenting Behavior and Children’s Eating Habits

The introductory module also includes an overview about why healthy eating is difficult for children and parents after cancer treatment. A summary of the six most common challenges is provided and it includes topics such as loss of appetite, taste changes, food aversions, steroids, limited exposure to new foods, and increased parental leniency for unhealthy foods and emotional feeding. A synopsis about common changes in children’s eating habits after cancer treatment is also provided to normalize parents’ experiences (eg, increased intake of junk foods and decreased intake of vegetables).

Following our modifications, the parent guidebook was assessed for readability using the Flesch-Kincaid Grade Level Test [24], yielding a grade level test score of 7.6 or a seventh to eighth grade school level. In concordance with the Australian National Framework for Consumer Involvement in Cancer Control [25], parents of CCS (N=4) were involved in reviewing the guidebook and providing feedback prior to publication.

### Primary and Secondary Outcome Measures

#### Demographic Information

Information on parent sex, age, education and employment status will be collected at baseline (T1, see Figure 1) together with the sex and age of the CCS. A validated emotion thermometers tool will also be used to assess participant distress and emotional state at the start of each intervention session [26]. This tool individually screens for emotional upset, anxiety, depression, and anger by asking the participant to rate each emotion on a scale of 0-10 (where 0 is none and 10 is extreme), and the level of assistance required to manage these emotions [26]. A participant will be deemed “distressed” if they score above seven on any of the thermometers [20], requiring facilitators to enquire about the participants available psychological supports (eg, current psychologist, general practitioner [GP], or social worker), and, if needed, will provide information for appropriate services including a 24-hour crisis hotline. The chief investigator will be contacted, and a nominated health professional will be contacted with the participant’s consent if appropriate.

